#### Virology outcome measures

Viral shedding is measured by RT-PCR test and is expressed in CT values or copies/ml. Data is generated at the Laboratory of Virology of the Geneva University Hospitals and will be entered to the e-CRF by the study nurses/physician or directly by the biologist in charge or a trained laboratory technician.Viability and infectiousness of the virus detected in the samples is measured by viral culture (expressed as a titer) at the Laboratory of Virology of the Geneva University Hospitals. Results will be entered to the e-CRF by the study nurses/physician or directly by the biologist in charge or a trained laboratory technician.

#### Safety outcomes

The incidence of serious adverse events unrelated to the natural course of influenza, serious adverse reactions, and suspected unexpected serious adverse reactions will be collected and reported following Swiss regulations. Reporting will be done by the sponsor investigator or by the co-investigators with the support of the CTU pharmacist.

#### Assessment of other outcomes of interest

Resistance mutations to baloxavir will be assessed by Sanger or whole genome sequencing. In case of Sanger sequencing, the partial sequence of 890–898 bp of the PA gene that we target includes all positions described to be associated with a decreased susceptibility (resistant) to baloxavir [19]. The screening and interpretation of the different mutations will be done through an algorithm co-developed between the Swiss national reference center of influenza and the Integrated database network system (Smartgene, Lausanne, Switzerland). The remaining respiratory samples, as well as the collected serum on admission and on discharge, will be conserved in a biobank located at the Laboratory of Virology of the Geneva University Hospitals.

### Plans to promote participant retention and complete follow-up {18b}

Subjects who withdraw or are withdrawn from the study prior to IMP administration will be replaced. No follow-up of these subjects will be performed, and no data will be analyzed. Subjects withdrawing or withdrawn after randomization and IMP administration will not be replaced. Data and samples collected before withdrawal will be analyzed. The reason for study discontinuation or deviation will be recorded in a specific section of the e-CRF.

Patients who drop out will be right censored at the time of withdrawal, with reasons for withdrawal documented. For deceased patients, clinical improvement will be considered as having never occurred until the end of follow-up: those patients will be right censored at 30 days.

### Data management {19}

Data management will be performed by the local Clinical Trial Unit (CTU) at the Geneva University Hospitals. The CTU is certified ISO 9001/2008, and the unit guarantees best practices in the field of clinical data management. Data are physically stored in secuTrial® using a dedicated CDMS software (Clinical Database Management System).

Data entry: To prevent data loss and preserve data integrity, all clinical and basic laboratory data will be directly entered into the e-CRF from the patients’ digital or paper-based medical records. All original data will be kept safely in the digital medical records system as well as in a dedicated, locked office with access only to study personnel. Virological data generated by the Laboratory of Virology at the Geneva University Hospitals will be entered into the e-CRF by the study nurse/physician. One hundred percent of primary outcome data will be checked by study monitors. Other data will be subject to regular random data consistency and correctness checks in the e-CRF by study monitors. Automatic value plausibility checks will be integrated into the e-CRF system.

Coding: All patient data will be coded in the e-CRF. Only personnel working closely on the project (PI, co-investigators, study nurses/physicians, study monitors) will have access to the uncoded data.

Data will remain accessible for authorized people throughout the study conduct and until the final publication of results.

Data security: Access to the patients’ digital medical records is controlled by the hospital in each recruiting center. Only authorized health care personnel can access the system. In our study, only the above-detailed study personnel will have access to the patients’ original digital and paper medical records. Access to the coded data on e-CRF is going to be strictly regulated as well. Only authorized personnel can enter or modify data; every data entry and modification will be automatically tracked.

Data storage: All data and applications are physically stored in dedicated data centers during 20 years on the Geneva University Hospitals’ premises.

For each set of data, quality control and triggers to computerized logic and/or consistency checks will be systematically applied to detect errors or omissions. After integration of all corrections in the complete set of data, the database will be locked and saved before being released for statistical analysis. Each step of this process will be monitored through the implementation of individual passwords and/or regular backups to maintain appropriate database access and to guarantee database integrity.

### Confidentiality {27}

The study investigator affirms and upholds the principle of the participant’s right to privacy and that they will comply with applicable privacy laws. Especially, the anonymity of the participants will be guaranteed when presenting the data at scientific meetings or publishing them in scientific journals.

Individual subject medical information obtained as a result of this study is considered confidential, and disclosure to third parties is prohibited. All patient data will be coded in the e-CRF.

Only personnel working closely on the project (PI, co-investigators, study nurses/physicians, study monitors) will have access to the uncoded data. Coding will be performed by the study team in each center. The identification key will be stored in a password-protected Excel file located on a secured server at each study site.

### Plans for collection, laboratory evaluation and storage of biological specimens for genetic or molecular analysis in this trial/future use {33}

Biological specimen collection is done by the study nurses and/or study physician, with sampling material provided by the sponsor. The use of coded labels corresponding to the randomization number upon biological specimen collection ensures patients’ privacy and specimen tracing. All biological specimens are handled and stored according to a dedicated standard operating procedure (SOP) at the respective hospital laboratories. Aliquots and leftover samples are stored at −80 °C at the sites and are sent at the end of each flu season to the Geneva University Hospitals’ Laboratory of Virology, where they are included in the study biobank before being analyzed in batch.

All leftover and serum samples taken for future research purposes will be stored for an indefinite duration (minimum 20 years) in the INFLUENT biobank located at the Geneva University Hospitals’ Laboratory of Virology.

Only coded samples from patients consenting will be used for future research purposes.

## Statistical methods

### Statistical methods for primary and secondary outcomes {20a}

The primary outcome (time to clinical improvement) is a time to event data. The “clinical improvement-free survival” will be estimated according to the Kaplan–Meier method and compared between groups (baloxavir vs. placebo) using a Cox model. The conditional effect of baloxavir on time to clinical improvement will be estimated with the following covariates included in the model (all collected at inclusion): age, vaccine status (yes/no), NEWS2 baseline score, BMI, and study site. As recommended by the EMA, the FDA, and ICH guidelines, we prospectively planned to include key prognostic factors as covariates in the statistical models, regardless of whether they were used for stratification during randomization. The purpose of this approach is to improve the precision of the estimated treatment effects and to account for potential imbalance in important baseline characteristics, even in randomized trials. Covariates that were not considered clinically relevant or did not demonstrate prognostic value based on prior knowledge were not included to avoid overfitting and preserve model parsimony.

First intention will be to include age and NEWS2 score as continuous variables. If the log-linearity assumption does not hold, age will be categorized as ≥65 vs. <65 years, and BMI (<30 vs. ≥30 kg/m^2^), and NEWS2 score as ≤7 vs. >7. This multivariable model will be considered the primary model. The study being a superiority trial, the principal analysis will be based on the intention-to-treat (ITT) population among all patients included in the trial independently of treatment timing POS. The same analysis will be done in the subgroup of patients receiving the study treatment ≤ 72 POS.

Clinical improvement-free survival will be estimated using the Kaplan–Meier method. For hypothesis testing, a Cox proportional hazards model will be employed. The hazard ratio (HR) will be estimated from the Cox model, and two-sided 95% confidence intervals will be derived using standard errors of the log (HR), calculated from the observed Fisher information matrix. The Breslow method will be used to handle tied event times. The proportional hazards assumption will be assessed visually using log(−log[survival]) plots. In case of a violation of this assumption, a secondary analysis will be conducted by incorporating time-dependent covariates to account for non-proportional effects.

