### Sample size {14}

Our hypothesis is that baloxavir treatment in adult, immunocompetent patients hospitalized for influenza will shorten the time to clinical improvement by at least 36 h compared to placebo. This 36-h difference was chosen as the minimal time difference considered to have a meaningful impact on clinical care. The median time to clinical improvement, in patients who received antivirals in a large clinical study, was about 4 days (97.5 h) [16]. The addition of the 36-h difference equals a time to clinical improvement of 5.5 days in the placebo group.

Two sample size calculations were performed. Sample size calculation no. 1 concerns all patients hospitalized for influenza (regardless of symptom duration at treatment administration): under the constant and proportional hazard assumption, median times to clinical improvement of 5.5 days in the placebo group and 4 days in the baloxavir group correspond to a hazard ratio of 1.375. With a follow-up period of 30 days, we calculated that a total number of 432 participants (216 per arm) would provide the trial with at least 90% power to detect such a baloxavir effect on time to clinical improvement at a two-sided significance level of 0.05.

Sample size calculation no. 2 concerns the subgroup of patients hospitalized for influenza with symptoms evolving for less than 72 h: under similar hypothesis (median times to clinical improvement of 5.5 days in the placebo group and 4 days in the baloxavir group, corresponding to a hazard ratio of 1.375 under the constant and proportional hazard assumption, and a follow-up period of 30 days), we calculated that a sample of 161 patients per arm would provide 80% power to detect a baloxavir effect in a subgroup analysis, at a two-sided significance level of 0.05. Assuming two out of three patients will present symptoms evolving for less than 72 h (ratio of 2:1), the study will need to include a total of 484 patients. With that sample size, the study will reach a power of 93% in the general population of hospitalized patients.

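### If log-linearity fails, the primary Cox model falls back on two-level splits of age, BMI and NEWS2, which gives back part of the precision that adjustment is meant to gain unless the true effects plateau or step near the cut-points

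*Protocol article*

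**What the plan says.** Section {20a} of the protocol article adjusts the Cox model for age, vaccine status, baseline NEWS2, BMI and site. On why it adjusts, it says "The purpose of this approach is to improve the precision of the estimated treatment effects", and it also mentions baseline imbalance.

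On functional form it says "First intention will be to include age and NEWS2 score as continuous variables"; BMI is not named in that sentence. The fallback is "If the log-linearity assumption does not hold, age will be categorized as ≥65 vs. <65 years", BMI below 30 against 30 or more, and "NEWS2 score as ≤7 vs. >7". Under either coding, "This multivariable model will be considered the primary model". The analysis is repeated in patients treated early after symptom onset, which is the co-primary objective.

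**The concern.** When a covariate effect is curved, the usual remedy is a form that can bend. A two-level split instead imposes a flat effect on each side of one cut and a jump at it. Unless the truth looks like that, the split captures less of the prognosis than a curve does, and often less than the straight line it replaces. In a Cox model, prognosis left uncaptured also moves the estimated conditional hazard ratio toward 1.

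The trial's own definitions give a reason to doubt the NEWS2 split in particular. Entry requires NEWS2 of at least 4, and the event is a score of 2 or less held for 24 h, or discharge. On the score route, a patient entering at 4 must fall 2 points and one entering at 7 must fall 5, yet the fallback treats scores 4 to 7 as identical.

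At stake is efficiency in the primary and co-primary tests, in exactly the situation where the fallback would be used.

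**Working it through.** **1. The plan's own figures.** The sample size section assumes medians of 5.5 days on placebo and 4 days on baloxavir, and 5.5/4 = 1.375, the hazard ratio it states. With exponential times and 30 days of follow-up, the event probability is 1 − (2^(−30/5.5) + 2^(−30/4))/2 = 0.986. Dividing the required events by 0.986 gives N:

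| Target | Events, Schoenfeld / Freedman | N | Plan |
|---|---|---|---|
| 90%, all patients | 415 / 422 | 421 / 428 | 432 |
| 80%, <72 h subgroup | 310 / 315 | 314 / 320 | 322 |

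Power at N = 484 is 93.6% or 93.2%, against 93% stated. The figures reproduce. They use no covariates, so the choice of coding does not affect them.

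**2. Information kept by a split.** For a normal covariate with a linear effect, a cut at standardised value z with proportion p below it keeps φ(z)²/[p(1−p)] of the variance. The distributions here are assumed.
- Age, mean 70, SD 15, cut 65: z = −0.333, 0.377²/(0.369 × 0.631) = 0.61.
- BMI, mean 27, SD 5.5, cut 30: z = 0.545, 0.344²/(0.707 × 0.293) = 0.57.

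**3. Simulation by covariate strength.** N = 322, conditional HR 1.375, placebo median 5.5 days, censoring at day 30, smooth curved effects of all three covariates, 1,500 replicates. Power:

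| SD of prognostic score | Split | Linear | Three-knot spline |
|---|---|---|---|
| 0.23 | 77% | 79% | 79% |
| 0.38 | 74% | 77% | 79% |
| 0.60 | 67% | 75% | 78% |

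A separate run of the same kind gave 75/79/81% at SD 0.38 and 66/75/77% at 0.60, with no clear difference at 0.23. For moderate and strong covariates, individual differences across the two runs are 3 to 11 points, or about 4 to 10 in round terms. In the strongest case the mean HR was about 1.32 to 1.33 with the split and 1.38 with splines.

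**4. Simulation by covariate shape.** Assumed: age and BMI as in step 2, and NEWS2 as 4 plus a negative binomial with mean 2.5. The flexible model used four-knot splines for age and BMI and linear plus quadratic NEWS2. There were 1,500 replicates, with a standard error near 1.1 points at power around 77%. Power at N = 322:

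| True shape | No adjustment | Split | Linear | Flexible | Split minus linear |
|---|---|---|---|---|---|
| Accelerating curve | 55.3 | 70.2 | 76.9 | 78.6 | −6.7 |
| Log-shaped | 68.5 | 74.6 | 79.7 | 80.1 | −5.1 |
| Steps away from the cuts | 63.4 | 66.2 | 70.7 | 74.2 | −4.5 |
| U-shaped age and BMI | 50.1 | 59.0 | 62.3 | 78.1 | −3.3 |
| Plateau near the cuts | 67.4 | 76.7 | 75.5 | 77.2 | +1.2 |
| Steps at the cuts | 62.7 | 79.7 | 72.9 | 73.7 | +6.8 |

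At N = 484 the pattern is the same: the split loses 2.5 to 5.2 points against linear terms in the first four shapes and gains 0.4 and 3.4 in the last two. The U-shape is the one case where the gap to flexible terms (19.1 points at N = 322) goes well beyond the range in step 3.

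**5. Type I error.** A rule that switches all three covariates to splits when a likelihood-ratio test on quadratic terms gives p < 0.05 had type I error of 4.1% to 5.3% at N = 484.

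**The case against.** Several objections are sound, and they limit the point.

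- **Shape.** A reader might infer that splitting always loses power against straight lines. It does not: it gains where effects step at 65 years and NEWS2 7. The documents give neither the shape nor the strength of the covariate effects.
- **Comparison with no adjustment.** The split beats the unadjusted model in every shape in step 4. In a further run (N = 322, smooth curves, 1,000 replicates), unadjusted/split/linear power was 76.7/78.4/80.0%, 68.0/73.7/77.4% and 59.2/68.1/75.9% for the three SDs. The split keeps roughly half the linear model's gain: 1.7 of 3.3, 5.7 of 9.4 and 8.9 of 16.7 points.
- **Planned power.** A reader might infer that the fallback drops the subgroup below its planned 80%. The plan's calculation is covariate-free, whereas the simulations set the conditional HR at 1.375, which makes the unadjusted HR smaller (about 1.28 at SD 0.60). Calibrated to an unadjusted HR near 1.375, the split gave 83.6, 82.3 and 86.4% and linear terms 83.6, 85.6 and 92.2%. The split forgoes extra precision; it does not undercut the plan.
- **Prespecification.** A reader might infer an uncontrolled, data-driven primary model. The covariates, the fallback form and all cut-points are fixed in advance, the analyst is blinded, and type I error stays near 5%. How log-linearity is judged is ordinary analysis-plan detail, and its absence from an article is not a fault.
- **Parsimony.** The article wants to avoid overfitting. That is a fair aim, but about three parameters against more than 300 events do not threaten it.

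What remains is that the stated remedy for curvature is usually less precise than an available alternative of similar simplicity.

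**Conclusion.** The point holds as one about precision. If the fallback is used and the true effects are smooth or U-shaped, the primary model gives back part of what adjustment gains. For smooth curves at N = 322, that ranges from almost nothing with weak covariates to about 4 to 10 power points with moderate to strong ones, with the conditional HR pulled toward 1. It is level or better only for plateaus or steps near the cuts.

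The sizes rest on assumed covariate distributions, shapes and strengths, on leaving out site and vaccine status (in the step 4 runs), and on all three covariates being split together. The article does not say whether one failing covariate switches the others, and switching only that one would cost less. The documents support no claim of error inflation or of wrong sample sizes.

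**What to change.** Replace the dichotomised fallback with a flexible form used from the outset in both the primary and co-primary analyses: three-knot restricted cubic splines, with knots at fixed quantiles, for age and BMI, and a spline or linear plus quadratic term for the discrete NEWS2 score. No log-linearity check then decides the primary model. Keep 65 years, 30 kg/m² and NEWS2 7 for descriptive tables only.

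The cost is wording plus about three extra parameters, against roughly 322 × 0.986 = 317 events in the subgroup at the planning rates. The downside is a loss against the splits if the true effects are steps exactly at the cuts: 2 points in one run at N = 322 (80% against 78%) and 6.0 in another (79.7% against 73.7%). Recruitment is planned through the 2026/2027 season and the analyst is blinded, so the change can be made before unblinding.

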### Outcomes {12}

#### Primary outcome

The primary outcome is time to clinical improvement (in hours), calculated from treatment administration until the measurement of a NEWS2 score ≤ 2 maintained for 24 h, or until hospital discharge, whichever comes first.

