a: 1/8 h up to 10 days. If hospitalization is longer and the primary endpoint is still not reached, decrease NEWS2 score measurements to 1/day up to discharge. b: only if requested by the treating physician. c: only CRP and white blood cell count will be collected and only twice during hospitalization, first at D0 and second if available between D2 and D4. d: ±1 day. e: only if RT-PCR positive with CT value compatible with viral growth (CT value < 30). f: depending on budget availability. (x): 6 ml, only at HUG, only consenting participants accepting blood sample collection for future research, timepoint of collection ± 1D. *: All SAE will be collected and reported in the annual safety report. SARS and SUSAR will be reported timely to the regulatory authorities

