## Data collection and management

### Plans for assessment and collection of outcomes {18a}

Primary outcome: We use the NEWS2 scoring system as a reliable and easily implementable method to evaluate disease severity at inclusion and to measure improvement in clinical status during follow-up. The primary outcome (NEWS2 score or hospital discharge) is recorded in the CRF once a day by dedicated study nurses. Components of the NEWS2 score are part of regular clinical management and therefore recorded by the team in charge of the patient during hospitalization. Death or ICU admission is not considered as discharge in the context of the primary endpoint. In case the patient is transferred to another hospital, it is considered as discharge regarding the primary endpoint. Transfers from the four participating university centers most often occur to rehabilitation hospitals, indicating that the patient no longer requires acute care for the influenza episode and is thus considered discharged.

To evaluate change in clinical status following treatment, we also use the 6-point ordinal clinical status severity scale. The remaining clinical outcomes include parameters which are easily measurable (need for O_2_ supplementation) or easily evaluable (need for antibiotic therapy for influenza complication, ICU admission, death). Influenza complications are retrieved from the discharge letter at the end of the hospital stay. The study nurses/physician collect the above data directly from the patients’ electronic medical records and enter it into the e-CRF. Clinical monitors will randomly check for data consistency and correctness.

Quality of life questionnaire EQ-5D-5L [17, 18] is filled out by the study nurses/physician on D0 and D90 post-treatment administration. At D90, the answers are collected by the study nurses/physician via the phone and are entered directly to the e-CRF. In case the patient is incapable of answering the questions, the questionnaire is not filled out.

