#### Definition of relevant intercurrent events

The estimand of interest targets the effect of treatment on the time to clinical improvement within 30 days of randomization. The variable is defined as the time (in days) from randomization to clinical improvement, with a maximum follow-up of 30 days. Death before improvement is considered an intercurrent event and will be handled using a composite strategy, whereby death is interpreted as a failure to improve. In this case, the time to improvement will be right censored at day 30. Other intercurrent events are considered irrelevant to the definition of the treatment effect and will be addressed using a treatment policy strategy, meaning that patients will be analyzed according to their randomized treatment regardless of these events.

The treatment effect will be summarized by the adjusted hazard ratio with corresponding 95% confidence intervals.

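### Breslow tie handling is fixed while the time unit is left open (hours or days): on a coarse grid it shrinks the hazard ratio slightly and costs 1 to 5 points of power, which Efron avoids at no cost

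*Protocol article*

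**What the plan says.** Section {20a} names the Cox model for hypothesis testing and states: "The Breslow method will be used to handle tied event times". Standard errors of the log hazard ratio are model-based, "calculated from the observed Fisher information matrix". The same analysis is applied to patients treated early after symptom onset ({20a} and {20b}), which is the co-primary objective in section {7}.

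Four statements bear on how many events will share a time:

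- Outcomes section {12}: "The primary outcome is time to clinical improvement (in hours), calculated from treatment administration".
- Definition of relevant intercurrent events: "The variable is defined as the time (in days) from randomization to clinical improvement, with a maximum follow-up of 30 days".
- Footnote a of Table 1, section {13}: "a: 1/8 h up to 10 days". If the stay is longer and the endpoint has not been reached, sites are to "decrease NEWS2 score measurements to 1/day up to discharge".
- Section {18a}: the primary outcome "is recorded in the CRF once a day by dedicated study nurses".

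Section {14} assumes medians of 5.5 and 4 days (hazard ratio 1.375) and 30 days of follow-up. It plans 161 per arm for 80% power in the <72 h group and 484 in total, for which it states 93% power overall.

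**The concern.** Breslow's approximation is accurate when few patients fail at the same recorded time. When a sizeable part of the risk set fails together, it pulls the log hazard ratio toward zero while the model-based standard error stays the same, so the test loses power. Nearly every patient in this trial is expected to have the event, and the endpoint is partly read at scheduled assessments, so ties could be heavy if times are stored coarsely. The analysis with least room is the <72 h one: it is sized at 80% with no allowance for dropout, and it is the reason the total rose from 432 to 484. The blinded re-estimation in {21b} checks only the median time and the <72 h prevalence, so it would not reveal this loss.

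**Working it through.** **Inputs.** From section {14}: medians 5.5 and 4 days, HR = 5.5/4 = 1.375, two-sided 0.05, 30 days. From section {8}: 1:1 allocation. From section {11c}: no loss to follow-up. From footnote a of Table 1: readings every 8 h to day 10, then daily.

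**1. The plan's own sample size.** Event probability by day 30 is 1 − 2^(−30/5.5) = 0.977 on placebo and 1 − 2^(−30/4) = 0.994 on baloxavir, mean 0.986.

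- Schoenfeld: events = 4(z_α/2 + z_β)²/(ln HR)². This gives 415 events (422 patients) for 90% power and 310 (316) for 80%.
- Freedman: events = (z_α/2 + z_β)²[(HR + 1)/(HR − 1)]². This gives 422 (430) and 315 (320).
- The plan states 432 and 322. Power at 484 is 93.6% (Schoenfeld) or 93.2% (Freedman), stated 93%. Also 322 × 1.5 = 483, stated 484.

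The plan's figures are reproduced within tolerance.

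**2. How heavy the ties could be.** Expected events: 484 × 0.986 ≈ 477. The share of those at risk who fail per interval is:

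- 8 h: 1 − 2^(−8/132) = 4.1% (placebo) and 1 − 2^(−8/96) = 5.6% (baloxavir).
- 24 h: 1 − 2^(−1/5.5) = 11.8% and 1 − 2^(−1/4) = 15.9%.

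**3. What differs between the methods.** With d failures tied at one time, Breslow uses the full risk-set sum S(β) for all d terms. Efron uses S(β) − (l/d)·S_D(β) for l = 0, …, d − 1, where S_D is the sum over the tied failures.

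**4. Simulation.** Exponential times from the plan's medians, censoring at 30 days, unadjusted Cox model, every event time rounded up to the grid, 10,000 replicates.

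| N | Grid | Breslow HR | Efron HR | Breslow power | Efron power |
|---|---|---|---|---|---|
| 484 | 1 h | 1.376 | 1.377 | 93.4% | 93.5% |
| 484 | 8 h to day 10, then daily | 1.362 | 1.377 | 92.4% | 93.5% |
| 484 | whole days | 1.346 | 1.376 | 91.1% | 93.4% |
| 322 | 1 h | 1.374 | 1.376 | 80.5% | 80.6% |
| 322 | 8 h to day 10, then daily | 1.361 | 1.375 | 78.7% | 80.6% |
| 322 | whole days | 1.344 | 1.375 | 75.8% | 80.4% |

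Log HR at N = 484: ln 1.3621/ln 1.3768 = 0.966 (3.4% smaller) and ln 1.3457/ln 1.3763 = 0.930 (7.0% smaller).

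A separate simulation gave, Breslow against Efron, 78.7% vs 80.4% (8-hourly/daily) and 77.5% vs 81.0% (whole days) at N = 322. At N = 484 it gave 91.8% vs 92.8% and 91.5% vs 93.6%.

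**5. Hand check, N = 322, whole days.** Power ≈ Φ[(mean log HR − 1.96 × model SE)/empirical SD].

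- Breslow: (0.2959 − 1.96 × 0.1138)/0.1062 = 0.69, about 75%.
- Efron: (0.3183 − 1.96 × 0.1138)/0.1143 = 0.83, about 80%.

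**6. Direction under the null.** In whole days (1,500 replicates) Breslow's type I error was 3.9% at N = 484 and 4.1% at N = 322, against 4.9% and 5.0% for Efron. The model SE exceeds the empirical SD (0.093 against 0.086 at N = 484 under the alternative), so the test is conservative.

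**7. Hours from each patient's own dose.** Suppose readings fall at fixed clock times and doses at varying times (an assumption). One simulation of 3,000 runs gave 80.9% (Breslow) vs 81.0% (Efron) at N = 322 and 92.9% for both at N = 484. Another gave 78.5% vs 78.8%, and 93.1% for both. Levels differ between simulations; the gap within each is 0.3 point or less.

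**The case against.** The strongest reply is that the coarse grid may never arise.

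- The outcome section already defines time in hours from dosing.
- The once-a-day CRF entry describes when nurses enter data. NEWS2 components are recorded by the ward team, and each reading can carry its own time.
- Days in the estimand section may be only a unit, since section {14} itself calls 97.5 h about 4 days.
- Daily readings affect only patients not yet improved at day 10: 2^(−10/5.5) = 28% of placebo and 2^(−10/4) = 18% of baloxavir patients under the plan's medians.
- Discharge also counts as the event and need not coincide with a reading. With 30% of events at discharge hours (assumed) on a strict 8-hour grid, the gap at N = 322 fell to 1.2 points.
- The primary model adjusts for five covariates; the simulations do not.
- Breslow is a standard, prespecified method, and its error here is conservative.

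All of this stands as a limit on size. It makes the loss conditional and rules out treating the whole-day figures as what the trial will see. It does not remove the point: the estimand section gives days from randomization, so the document does not secure the hourly scale, and on no grid examined did Breslow do better than Efron.

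A reader might infer that the <72 h analysis has about 76% power and that the primary estimate will be 7% too small on the log scale. The documents do not support that, because it needs rounding to whole days, which no section prescribes.

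**Conclusion.** The point holds in conditional form. Breslow is fixed without a reason, beside two conflicting definitions of the time variable.

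- **Strict 8-hourly-then-daily grid:** HR about 1.36 for a true 1.375, 1 to 2 points of power lost, <72 h analysis at about 79%.
- **Whole days:** HR about 1.35, 2 to 5 points lost, <72 h analysis at about 76 to 77%.
- **Hours from each patient's own dose:** negligible.

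The overall analysis keeps more than 90% power in every case. No false-positive risk follows, and it would be wrong to infer that the test is invalid or that the overall comparison is underpowered.

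The figures assume exponential times, no deaths or dropout, no covariates, and every event on the grid; the last makes them upper-end as far as ties go. Shape matters too: with a rising hazard (Weibull shape 1.5) a smaller simulation gave Breslow/Efron log-HR ratios of 0.966 (8 h) and 0.904 (24 h), against 0.976 and 0.930 for exponential times. This is a free improvement to a stated method, not a flaw that threatens the trial.

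**What to change.** In {20a}, replace Breslow by Efron for the primary Cox model, and let {20b} follow. Reconcile the outcome section with the estimand section so that one origin and one unit apply, with time analysed in hours at the actual time of the reading or discharge, and make sure the CRF captures those times. Either step alone removes most of the loss; together they make the result independent of how times are stored.

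The cost is one word, one software option and one corrected definition. It needs no extra patients, and in the simulations Efron's type I error stayed at about 5%. Make the change before unblinding, so that the choice of tie method cannot look data-driven.
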